### Handling missing data

3.2

To thoroughly analyze missing data we will use a combination of graphic inspection with missing data matrix plots and bar charts, calculate frequencies and percentages of missing data for each variable at every time point and use the Little’s test (61). This will enable us to determine the extent of the missingness in our dataset and its nature (missing completely at random or more systematic). In our estimation of possible patterns we will take all the available information into account, like the detailed records that are kept of individual participants during data collection, the COVID-19 pandemic, symptom severity, etc. We intend to use multiple imputation, if this is indeed the most optimal method to handle missing data in our study. Multiple imputation is statistically the most accurate way of dealing with missing data (62). The results of the analyses in 20 imputed datasets will be pooled. We will only delete cases from the analyses when there is too much data (≥50%) missing for multiple imputation. For the linear mixed model analyses we will use the original, unimputed dataset, because these statistical analyses can deal with missing values. The information about missing data in the study will be reported in detail, using the Strengthening the Reporting of Observational Studies in Epidemiology (STROBE) statement for observational studies (63).

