#### Baseline screening

2.6.7

We use the Screener for Intelligence and Learning disabilities (SCIL), which is a valid and reliable screening questionnaire developed to detect an intelligence quotient of ≤ 84, indicated by a cut-off score of 19 or lower (60). Out of consideration for clients’ wellbeing and the validity of the results, clients are offered to stop the interviews or complete only part of the measurements when they have a SCIL score <20, show difficulty understanding the measurements, or seem too distressed.

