#### Short and long term effects of DBT-PTSD

3.1.1

To study short-term within-subjects differences, change scores will be calculated with the first three time points (T2-T1=Δtreatment and T1- T0=Δwaiting-list), resulting in four Δ-variables for PTSD, six for dissociation, two for NNSI and suicidal ideation and two for borderline symptomatology. Two-sided paired-samples t-tests will be conducted to compare the Δtreatment and Δwaiting-list scores. We use two-sided tests to maintain a conservative α level. When the anticipated waiting list period turns out to be less than three months, we will consider excluding the participant from the paired t-test analyses. When, at the end of the study, the waiting list period appears to vary much more than expected, and we might need to exclude too many patients, we will consider alternative statistical analyses that are able to deal with this variability, such as linear mixed model analysis. *Post-hoc* analyses to assess long term treatment effects in PTSD, dissociation, NNSI and suicidal ideation, and borderline symptomatology will be carried out with linear mixed model analyses with time as random effects. We will include two predictors of treatment effects on PTSD severity, as measured with the CAPS-5 and PCL-5 into the PTSD model: 1) baseline severity of BPD symptoms (using the total score on the BPDSI) and 2) cluster C personality disorders (with the sum of the dimensional SCID-5-P scores of the three cluster C personality disorders). Further, we will use linear mixed model analyses to study the effects of DBT-PTSD on social functioning and quality of life over time.

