#### Symptom trajectories with diary data

3.1.2

Finally, as more explorative objectives, we intend to study symptom trajectories on a group and individual level with the diary data. We will use linear mixed model analyses and graphs to show symptom trajectories over time with PTSD intrusive symptoms, emotion dysregulation behaviors (non-suicidal self-injury, high risk behavior, binge eating or self-induced vomiting, alcohol use, drugs/medication use, anger, other problem behavior), suicidality, hours of sleep, happiness and undertaking pleasant activities. Linear mixed model analyses are capable of handling missing data, even when a substantial part of the data is missing. We hypothesize that when PTSD symptoms decrease, improvements on the other variables will follow. To test this hypothesis, we will include PTSD symptoms as a time-varying covariate with a two week lag in our linear mixed models.

Second, we study the degree to which clients invest in their treatment, operationalized by the DBT-PTSD diary items: ‘time spent on therapeutic assignments’ (in minutes) and ‘exposure assignments carried out’ (yes/no), as predictors of treatment outcome. We will use the CAPS-5 and PTSD symptoms of the diary to measure change in PTSD symptoms and the diaries emotion dysregulation behavior items for emotion dysregulation. We hypothesize that clients who are motivated and invest in their treatment, by doing more exposure assignments and spending more time on therapeutic assignments, will benefit more from DBT-PTSD. To test this hypothesis, we will split the sample in half to compare clients with the highest and lowest scores on homework and exposure assignments during the first four weeks and over the whole course of treatment. We will again use linear mixed model analyses with a time x group interaction in our model.

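### The reason for leaving all mixed-model data unimputed covers missing outcomes only; a missing BPDSI, SCID-5-P or lagged diary covariate still removes clients or rows

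*Protocol article*

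**What the plan says.** Section 3.2 intends multiple imputation with 20 datasets, provided it proves the best method, and then exempts the mixed models: "For the linear mixed model analyses we will use the original, unimputed dataset, because these statistical analyses can deal with missing values". Section 3.1.2 makes the same claim for the diary models: "Linear mixed model analyses are capable of handling missing data, even when a substantial part of the data is missing". Neither sentence is limited to missing outcomes, and neither gives a rule for a missing covariate.

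Some of these models contain covariates that can be missing:

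- Section 3.1.1: "We will include two predictors of treatment effects on PTSD severity, as measured with the CAPS-5 and PCL-5 into the PTSD model". The two are the baseline BPDSI total score and a cluster C score, formed "with the sum of the dimensional SCID-5-P scores of the three cluster C personality disorders".
- Section 3.1.2: the diary models will "include PTSD symptoms as a time-varying covariate with a two week lag".

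Two other statements bear on the point. Section 2.6.7 says that, when the SCIL score is below 20, or a client has trouble understanding the measures or seems too distressed, "clients are offered to stop the interviews or complete only part of the measurements". Section 3.2 says of deletion: "We will only delete cases from the analyses when there is too much data (≥50%) missing for multiple imputation".

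**The concern.** A likelihood-based mixed model uses every observed outcome and is valid under missing at random for the outcomes that are absent. It conditions on the covariates, however, and has no model for them. Standard R fits omit any row with a missing covariate. Both PTSD predictors are fixed over time, so one missing value takes out all of a client's rows, including CAPS-5 and PCL-5 scores that were observed.

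The stated reason for not imputing therefore fails in the models where covariates can be missing. At stake are precision for the predictor question and the representativeness of the clients who remain. If the long-term PTSD effects are read from the model that holds the predictors, those effects would also rest on clients who completed both interviews.

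**Working it through.** **The plan's own figure.** Section 2.8 gives N=51 for a paired t-test (difference 0.5 SD, α=.01, power .80). Exact noncentral-t power, two-sided, is .799 at n=50 and .809 at n=51, so 51 reproduces. Adding 10% gives 51 × 1.10 = 56.1, against the stated 56. This figure is not in dispute; 56 is used below as the number of clients.

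**Missing outcome against missing covariate.** 56 clients × 5 assessments (T0–T4) = 280 rows. Suppose 8 clients are incomplete:

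- Outcome missing at T3 and T4: 280 − 8 × 2 = 264 rows, all 56 clients kept.
- Only the baseline predictor missing: 280 − 8 × 5 = 240 rows, 48 clients kept.

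**Clients left in the predictor model.** The documents give no missing rate, so m, the share of clients lacking each predictor, is an assumption. If both are missing in the same clients, the kept fraction is 1 − m; if missing independently, it is (1 − m)². The standard error grows roughly by 1/√(kept fraction).

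| m (assumed) | Together: kept of 56 | SE | Independent: kept of 56 | SE |
|---|---|---|---|---|
| 5% | 53.2 | +3% | 50.5 | +5% |
| 10% | 50.4 | +5% | 45.4 | +11% |
| 15% | 47.6 | +8% | 40.5 | +18% |

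A client who stops an interview session is likely to lack both scores, so the left-hand columns may be nearer the truth.

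**Bias.** If a fraction f is dropped and those clients improve by δ points less than the rest, the mean change is overstated by f × δ. The documents supply neither f nor δ.

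**Lagged diary model.** Twelve weeks are 84 days; a 14-day lag leaves at most 84 − 14 = 70 usable days. If rows are single days and a share p is missing independently, 70 × (1 − p)² remain: 44.8 at p = 20% and 34.3 at p = 30%. If missing days coincide fully across the lag, 70 × (1 − p) remain: 56 and 49. Both the daily rows and the values of p are assumptions.

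**Against the deletion rule.** A client lacking one or two predictor scores can be well below 50% missing, yet leaves the predictor model entirely. That does not sit with the section 3.2 statement that only cases at or above that threshold are deleted.

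**The case against.** The reach is limited. The paired t-tests are to use multiple imputation, and mixed models with time alone are untouched. The article itself calls the predictor and diary aims exploratory. This stands.

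A reader might infer from section 2.6.7 that the predictors will be missing, and not at random. The documents do not show this. The section makes a conditional offer, gives no rate and does not say which instruments are left out. Missingness tied to a recorded SCIL score need not be missing not at random, and a complete-case fit is biased only if missingness depends on the outcome given the model's covariates. What survives is that missing predictors are foreseeable and probably not completely at random, since the reasons for stopping relate to the client's condition.

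A reader might also infer a long-term effect overstated by about 1 CAPS-5 point. That takes independent 10% missingness (f = 1 − 0.9² = 0.19) and an assumed 5-point difference: 0.19 × 5 = 0.95. With both predictors missing together it is 0.10 × 5 = 0.5, and the 5 points have no source in the documents.

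It is also fair to say that section 3.1.1 does not rule out a PTSD model without predictors, that section 3.1.2 does not say whether diary rows are days or longer summaries, and that row deletion is a software default rather than a stated step. The 50% rule is worded with imputation in mind. Section 3.2 already plans missingness counts for every variable and time point, which goes some way towards reporting the loss. None of this repairs the stated reason, which settles the dataset for all mixed models on a ground that is true only for outcomes.

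**Conclusion.** The point holds in a limited form. The rationale in section 3.2 is too broad, and the dataset it fixes is unsuitable for models with incomplete covariates. Affected are the BPD and cluster C predictor models, the lagged diary models, and the post-hoc long-term PTSD effects if these come from the model with the predictors.

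Under assumed missing rates of 5% to 15% per predictor, between about 53 and 40 of 56 clients remain and standard errors rise by 3% to 18%, depending on the rate and on whether the two scores go missing together. No size can be put on bias from the documents, and a reading that the main treatment comparison is compromised is not supported. The correction is worth making because it is cheap and the error is in a stated rule, not in detail left to a fuller plan.

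**What to change.** 1. In section 3.2, limit the sentence to missing outcomes and add a rule for missing covariates. Align section 3.1.2 with it.
2. Estimate long-term PTSD effects in a mixed model without the two predictors, on the unimputed data.
3. Fit the predictor models on multiply imputed data (20 datasets, pooled). The imputation model should hold both predictors, the T0–T4 CAPS-5 and PCL-5 scores and any time-by-predictor terms. Give the complete-case result as a sensitivity analysis.
4. For the lagged diary model, impute the lagged score with a multilevel method, or report the rows lost.

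The cost is analysis-plan wording and some extra programming. Section 3.2 makes multiple imputation conditional, so the imputed datasets cannot be taken as certain to exist; the predictor models need them in any case. The small downside is that the predictor results will then depend on the imputation model, which the complete-case analysis makes visible.

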### Economic evaluation of DBT-PTSD

3.3

We will perform a cost-effectiveness and cost-utility analysis from a societal perspective. We calculate healthcare costs and productivity loss over the past three months (measured with the Tic-P), using standard unit cost units as described in the Zorginstituut Nederland (ZiN) guidelines (64). Outcomes consist of PTSD severity (measured with the CAPS-5) and quality-adjusted life-years (QALY’s), which will result in two Incremental Cost-Effectiveness Ratios (ICERs): additional costs for one point improvement in PTSD severity and additional costs per Qaly. Parallel to the analysis of effectiveness, in the cost-effectiveness analysis we also compare within-subjects: intervention versus waiting list. To obtain an estimate on longer-term cost-effectiveness, costs and effects of inpatient DBT-PTSD will be extrapolated from the six and twelve month follow-up data to a five year outcome, using four different scenario’s to gain insight into the upper and lower limits of the actual cost-effectiveness: 1) Care consumption and PTSD severity will remain what they were during the last six months follow-up; 2) Care consumption and PTSD severity are (back) at baseline levels immediately after the end of 1 year follow-up (pessimistic); 3) Care consumption and PTSD severity will gradually decrease after the follow-up has ended, with 25% in total over five years (optimistic); 4) Care consumption and PTSD severity will gradually increase again (after initial reduction) after the follow-up ends, until the baseline levels are reached, linear in five years (moderately pessimistic). Bootstrapping and cost-effectiveness acceptability curves (CEAC) will be used to quantify the uncertainty around the ICERs. We will use the CHEERS 2022 statement in reporting our outcomes (65).

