### Measurement instruments

2.6

An overview of all measurements is provided in **Figure 2** and shows which measures are part of ROM at the treatment center. Treatment history is assessed at baseline. At follow-up, we register treatments that clients received after inpatient DBT-PTSD.

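### The four five-year cost-effectiveness scenarios tie care use to PTSD severity, so they miss the limits they are meant to show if care use at follow-up is above baseline

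*Protocol article*

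**What the plan says.** Section 3.3 (Economic evaluation of DBT-PTSD) carries costs and effects forward from the six- and twelve-month follow-up to five years. It uses four scenarios, "to gain insight into the upper and lower limits of the actual cost-effectiveness":

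- Scenario 1 reads "1) Care consumption and PTSD severity will remain what they were during the last six months follow-up".
- Scenario 2, labelled pessimistic, puts both quantities at their baseline values as soon as the one-year follow-up is over.
- Scenario 3, labelled optimistic, lets both decline step by step, by 25% overall.
- Scenario 4, labelled moderately pessimistic, reads "4) Care consumption and PTSD severity will gradually increase again (after initial reduction) after the follow-up ends, until the baseline levels are reached", along a straight line.

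The outcomes are two ratios: "additional costs for one point improvement in PTSD severity and additional costs per Qaly". Bootstrapping and acceptability curves are to describe the uncertainty around them.

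On care after discharge, section 2.6 says "At follow-up, we register treatments that clients received after inpatient DBT-PTSD", and section 2.6.5 says that the TiC-P records care in the waiting period, during the admission and afterwards. Neither section says how much care is expected.

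**The concern.** In every scenario one rule governs both the cost driver and the effect. That spans the extremes only if a lower level of care at follow-up accompanies the lower severity. The plan takes this for granted: scenario 4 has care going up again after a first reduction ("Care consumption and PTSD severity will gradually increase again (after initial reduction) after the follow-up ends"), and scenario 2 counts a return to baseline as bad news on both sides.

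If clients use more care after discharge than before treatment, a return to baseline care saves money. Scenario 2 then joins the worst effect to a favourable care cost. No scenario holds the combination of relapse with continuing high care use, nor that of lasting benefit with care back to its earlier level. At stake is the span that readers will take as the limits of five-year cost-effectiveness for an expensive 12-week admission.

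**Working it through.** The article states no result for the scenarios, so there is no figure to reproduce. The check has a general part, which needs no assumed levels, and two illustrations, which do.

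**Notation.** c0 and c1 are yearly care costs at baseline and at follow-up. s1 is CAPS-5 severity at follow-up and g > 0 the gain from baseline. H is the number of extrapolated years and v > 0 the value of one CAPS-5 point-year. f is the mean level under the 25% decline, as a fraction of the follow-up level. r, between 0 and 1, is the mean share of the follow-up difference kept while drifting back. The first year is common to all scenarios and drops out. Net benefit after year 1 = v × effect − cost, both against baseline:

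- S1: [v·g − (c1 − c0)]·H
- S2: 0
- S3: [v·(g + (1 − f)·s1) − (f·c1 − c0)]·H
- S4: r·[v·g − (c1 − c0)]·H

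**Care at or below baseline (c1 ≤ c0).** Baseline is the dearest care path and the worst severity path; the decline is the cheapest care path and the best severity path. S2 and S3 are therefore the minimum and maximum of all 16 care-by-severity pairs. The plan does what it says.

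**Care above baseline: unfavourable limit.** Pair care held at c1 with severity back at baseline. Net benefit is −(c1 − c0)·H. The four scenarios exceed it by:

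- S1: v·g·H
- S2: (c1 − c0)·H
- S3: v·(g + (1 − f)·s1)·H + (1 − f)·c1·H
- S4: r·v·g·H + (1 − r)·(c1 − c0)·H

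All are positive. This limit is missed for any excess and any positive v.

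**Care above baseline: favourable limit.** Pair baseline care with declining severity. This beats S3 only if c0 < f·c1, that is c1/c0 > 1/f.

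- Decline completed within the extrapolated years: f = 0.875, and 1/0.875 = 1.14.
- Decline spread over five years after follow-up, four of them counted: mid-year reductions 2.5, 7.5, 12.5 and 17.5%, mean 10%, f = 0.90, and 1/0.90 = 1.11.

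Below an excess of about 11–14% this limit still holds.

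**Illustration 1, net benefit.** Assumed: c0 = 100 per year, CAPS-5 45 falling to 30, v = 5, H = 4, f = 0.875, no discounting, no productivity costs.

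| c1 | Four scenarios | All 16 pairs |
|---|---|---|
| 80 | 0 to 495 | 0 to 495 |
| 110 | 0 to 390 | −40 to 390 |
| 130 | 0 to 320 | −120 to 375 |
| 200 | −100 to 75 | −400 to 375 |

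For c1 = 130: S3 = 5 × 18.75 × 4 − (113.75 − 100) × 4 = 375 − 55 = 320; care held with relapse = −30 × 4 = −120. At c1 = 200 the labels also fail: S2 (0) does better than S1 (−100) and S4 (−50).

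**Illustration 2, cost ratio.** Assumed: admission 100 units, CAPS-5 40 falling to 25, effect in point-years, care 50% above baseline already in year 1, years 2–5 at mid-year values, f = 0.90, no productivity costs. With c0 = 10 and c1 = 15:

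- S3: cost 100 + 5 + 4 × (13.5 − 10) = 119; effect 15 + 4 × 17.5 = 85; ratio 1.40, the lowest of the four.
- S2: 105/15 = 7.00, the highest of the four.
- Care at baseline, severity declining: 105/85 = 1.24.
- Care held, severity at baseline: 125/15 = 8.33.

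With c0 = 20 and c1 = 30 the four scenarios run from 138/85 = 1.62 to 110/15 = 7.33, and the separated pairs from 110/85 = 1.29 to 150/15 = 10.0. The true maximum exceeds the highest scenario by 19% (8.33/7.00) and 36% (10.0/7.33). The true minimum lies 12% (105/119) and 20% (110/138) below the lowest. With care 100% above baseline, the maximum is exceeded by 36% (150/110) and 67% (200/120).

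**The case against.** The strongest reply is that the condition may never arise. The Introduction says that the economic burden grows with severity and complexity, clients enter with severe PTSD, and usual treatment may continue while they wait. Care use may well fall, and then the four scenarios are sufficient. This stands: the point is conditional.

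A reader might infer from section 2.6 that more care after discharge is expected. The text does not support that. It says only that such treatments are registered, and section 4.1 gives the reason: other influences on the follow-up measurements.

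A reader might also conclude that the range is too narrow at both ends whenever care exceeds baseline. That goes too far: up to an excess of about 11–14% only the unfavourable end is missed. Nor does the article promise strict bounds; it speaks of gaining insight into limits.

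The analysis is societal, and the illustrations leave out productivity loss. If that loss returns to baseline on relapse, scenario 2 may still be pessimistic on total cost. The missed limit remains, however: if productivity follows severity, the separated pair and scenario 2 carry the same productivity cost and still differ by (c1 − c0)·H.

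Bootstrapping and acceptability curves do not answer the point. They describe sampling uncertainty within a scenario, not the tie between cost and effect.

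**Conclusion.** The point holds in conditional form. With care use at follow-up at or below baseline, the four scenarios bound the result. With care use above baseline, they omit the unfavourable limit for any excess and the favourable limit beyond about 11–14%. Scenario 2 is then not pessimistic on care costs, and the rise described in scenario 4 cannot be applied to care at all. The unfavourable-limit result needs only that severity has improved at follow-up and that a CAPS-5 point has positive value. It carries over to cost per QALY if utility follows severity.

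The size in this study is unknown, because the documents give neither care costs nor CAPS-5 levels. The 19–36% shortfall at the upper end and 12–20% at the lower end are illustrations that rest on the assumptions listed. It would be wrong to read them as an error already present in the study's results. This is a moderate weakness in an extrapolation that serves the article's fourth objective; it does not touch the primary analysis of PTSD severity.

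**What to change.** Keep the four scenarios as reference cases and add at least two that separate the paths: (a) care remains at its follow-up level while severity returns to baseline; (b) care returns to baseline while severity is held or keeps improving. Crossing the four care paths with the four severity paths (16 cells) also works but is not essential. Report the minimum and maximum over these scenarios as the explored range, and assign the labels *optimistic* and *pessimistic* according to the observed direction of the cost difference. State over how many years the 25% decline runs. Fix the added scenarios before cost results are seen, so that they are not chosen after the fact.

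The cost is a few lines of code and a slightly larger table, with no new data. The downside is a wider and less favourable range.
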